## Abstract

**Background:**

Patients who undergo tracheostomy often experience respiratory muscle dysfunction and reduced airway clearance capacity, leading to reduced quality of life. While inspiratory muscle training (IMT) is effective at improving respiratory outcomes among mechanically ventilated patients, evidence about its clinical utility and safety, especially in tracheostomized populations, is limited. Moreover, the optimal IMT protocol for this patient cohort remains undefined. The aim of this study is to evaluate the effects of high-intensity interval inspiratory muscle training (HI-IMT) on diaphragmatic function, airway clearance capacity, anxiety levels, decannulation rates, quality of life, and safety outcomes among tracheostomy patients.

**Methods:**

This is a single-center, single-blind, randomized controlled trial. Seventy tracheostomized patients (aged 40–70 years, with tracheostomy for 1–3 months) will be randomly assigned to either the HI-IMT group or the control group. The HI-IMT group will receive IMT at 50% of the maximal inspiratory pressure (MIP), 30 breaths/day, 5 days/week for 2 weeks. The control group will receive sham training, which will involve performing the same breathing cycles without any applied resistance. Both groups will receive standard care, including pharmacological therapy, rehabilitative nursing, and basic rehabilitation exercises. Diaphragmatic function, airway clearance ability, anxiety levels, and quality of life will be assessed using the MIP% predicted (primary outcome) and peak inspiratory flow (PIF), the Semi-Quantitative Cough Strength Score (SCSS), the standardized Zung Self-Rating Anxiety Scale (SAS), and the Tracheostomy-Specific Quality of Life (TQOL) scale. Additionally, decannulation rates and adverse events will be systematically recorded throughout the study period. Data will be analyzed using parametric or non-parametric tests for unadjusted between-group comparisons. All analyses will adhere to the intention-to-treat principle, with a *p*-value < 0.05 set for statistical significance.

**Discussion:**

This study is expected to provide valuable evidence about the efficacy and safety of HI-IMT in improving diaphragmatic function and overall outcomes among tracheostomized patients. These findings may contribute to the development of standardized respiratory rehabilitation protocols tailored to this patient population.

**Trial registration:**

Chinese Clinical Trial, ChiCTR2500099091. Registered on 18 March 2025. https://www.chictr.org.cn/bin/project/edit?pid=265948.

**Supplementary Information:**

The online version contains supplementary material available at 10.1186/s13063-025-09334-3.

## Administrative information

Note: the numbers in curly brackets in this protocol refer to SPIRIT checklist item numbers. The order of the items has been modified to group similar items (see http://www.equator-network.org/reporting-guidelines/spirit-2013-statement-defining-standard-protocol-items-for-clinical-trials/).

## Introduction

### Background and rationale {6a}

Tracheostomy is a critical intervention for maintaining airway patency in critically ill patients [1]. Epidemiological data indicate that approximately 13% to 35% of these individuals undergo tracheostomy during intensive care treatment [2–4]. However, this procedure disrupts normal respiratory physiology, leading to diaphragmatic weakness, diminished cough effectiveness, and increased risk of pulmonary infections [5–7]. These complications are associated with delayed decannulation, prolonged hospitalization, and reduced overall quality of life [8].

In current clinical practice, respiratory rehabilitation for tracheostomized patients relies primarily on traditional methods, such as abdominal (diaphragmatic) breathing, pursed-lip breathing, candle-blowing exercises, paper strip resistance training, manual hyperinflation technique, or use of incentive spirometers [9–11]. However, these approaches often do not allow accurate assessment of respiratory muscle strength and fail to provide personalized training protocols. Since respiratory muscles are part of the skeletal muscle system, exercises to strengthen them should adhere to the principle of overload [12]. Nonresistive training modalities may not be sufficient to fully enhance patient lung function [13–15].

Inspiratory muscle training (IMT), which specifically targets the diaphragm and accessory inspiratory muscles, has demonstrated efficacy in mechanically ventilated patients [16]. A systematic review including 28 studies (*n* = 1184) confirmed that IMT increases inspiratory muscle strength and facilitates earlier weaning from mechanical ventilation in intensive care settings [17]. Nevertheless, most available evidence pertains to intubated patients, and there are limited data specific to tracheostomized populations [18–22]. Importantly, tracheostomy alters respiratory mechanics, such as by reducing airway resistance and impairing the generation of negative inspiratory pressure, requiring tailored training approaches. Furthermore, the use of conventional threshold-loading devices in tracheostomized patients has disadvantages, including ceiling effects and mismatches between pressure and volume during high-resistance training [23, 24].

The POWERbreathe KH2 is a novel inspiratory muscle training device that uses tapered flow resistive loading (TFRL), potentially overcoming the limitations of traditional threshold loading (TL) methods [25]. Unlike TL, TFRL introduces an initial threshold followed by a velocity-dependent decline in resistance, resembling isokinetic training of the musculature of the limb [23, 26, 27]. This configuration minimizes pressure-volume conflicts and enables real-time monitoring of inspiratory pressure and flow, thereby allowing precise dosage adjustments. Preliminary case studies and small-sample investigations suggest that the device is safe and feasible for use with tracheostomized patients, although robust evidence from randomized controlled trials is currently lacking [28, 29].

Moreover, the optimal IMT protocol for tracheostomized individuals remains to be established. As tracheostomized patients often have weak inspiratory muscles, they are unlikely to tolerate sustained loading of the respiratory muscles without distressing fatigue. High-intensity interval inspiratory muscle training (HI-IMT), which is characterized by high-intensity and low-repetition protocols, represents a promising therapeutic strategy for this population. This modality can optimize therapeutic efficacy while minimizing treatment-induced discomfort. This approach has been used successfully in numerous trials [30–33].

### Objectives {7}

The primary objective of this study is to evaluate the efficacy of HI-IMT in improving the diaphragmatic function of patients undergoing tracheostomy. The secondary objectives include investigating the effects of HI-IMT on airway clearance capacity, anxiety levels, quality of life, decannulation rates, and safety outcomes.

### Trial design {8}

This is a single-center, randomized, single-blind, parallel-group, exploratory clinical trial. A total of 70 tracheostomized patients will be enrolled and randomly allocated at a 1:1 ratio to either the HI-IMT intervention group or the control group. The study procedure is shown in Fig. 1.

**Fig. 1 Fig1:**
[figure not shown]
Flow chart of the study

## Methods: participants, interventions, and outcomes

### Study setting {9}

This study will be conducted at the Sixth Affiliated Hospital of Sun Yat-sen University. All the evaluations and training sessions will take place either in the rehabilitation medicine treatment room or at the patient’s bedside, depending on individual clinical needs.

### Eligibility criteria {10}

Inclusion criteria:Patients aged 40–70 years;Patients undergoing tracheostomy for 1–3 months, with a daily suction frequency of ≥ 10 times and MIP% predicted ≤ 30%;Patients with a 7.5 mm diameter tracheostomy tube;Patient with stable vital signs and who are conscious, cognitively intact, and able to understand and cooperate with training, achieve a score of 5 on the Standardized Five Questions (S5Q) [34];Patients without evidence of airway collapse or stenosis confirmed by fiberoptic bronchoscopy;Patients with oxygen saturation (SpO₂) ≥ 93% on room air, respiratory rate ≤ 25 breaths/min, blood pressure between 90 and 180 mmHg, heart rate between 60 and 120 beats/min, and body temperature between 36.5 and 38.5 °C;Patients who are willing to participate in the study and provide signed informed consent.

Exclusion criteria:Patients with a metal tracheostomy tube, other non-cuffed tracheostomy tubes, or fenestrated tubes;Patients with a diagnosis of progressive neuromuscular disease;Patients with a contraindications to IMT, including rib fractures, pulmonary bullae, or acute asthma exacerbation;Patients with unhealed tympanic membrane perforation, other significant ear disorders, or evidence of aspiration;Patients with severe comorbidities affecting major organ systems, such as severe cardiac dysfunction (NYHA Class III/IV heart failure), severe hepatic insufficiency (Child-Pugh class B/C), or end-stage renal disease requiring dialysis;Patients for whom suctioning is required more frequently than once per hour.

### Who will obtain informed consent? {26a}

A designated member of the research team will provide each eligible participant with a comprehensive explanation of the study’s objectives, procedures, potential risks and benefits, and any expected discomfort. The participants will be clearly informed that their involvement is entirely voluntary and that they may withdraw from the study at any time without any impact on their future medical care or treatment. Written informed consent will be obtained using an ethics committee–approved consent form prior to the initiation of any study-related procedures.

### Additional consent provisions for the collection and use of participant data and biological specimens {26b}

Not applicable, as no biological samples will be collected or stored for this study.

## Interventions

### Explanation for the choice of comparators {6b}

The control group will undergo placebo inspiratory muscle training (IMT) using the same POWERbreathe KH2 device as the HI-IMT group; however, no resistance load will be applied. The participants in both groups will receive standard medical care, as detailed in item 11a.

### Intervention description {11a}

#### Conventional medical interventions

Conventional medical interventions include pharmacological treatment, rehabilitation nursing, physical therapy, and dysphagia management. Pharmacotherapy includes the administration of anti-infectives, mucolytics, and nutritional support, as well as the regulation of electrolyte balance [35]. Rehabilitation nursing involves airway humidification, tracheal suctioning, oral hygiene, and monitoring of tracheal cuff pressure. Physical therapy integrates postural drainage, percussion techniques, and the active cycle of breathing technique (ACBT), which are typically delivered in 20-min sessions. Dysphagia management includes neuromuscular electrical stimulation (NMES) to enhance pharyngeal constriction, along with orofacial sensory–motor training to improve swallowing coordination, which are also administered in 20-min sessions.

#### HI-IMT group

In addition to conventional care, participants in the HI-IMT group will receive inspiratory muscle training under the guidance of a trained physiotherapist using the POWERbreathe KH2 device (Fig. 2). Prior to the intervention, the MIP will be measured with the tracheal cuff inflated to ensure accurate loading. A wet heat exchanger will be connected between the tracheostomy site and the POWERbreathe KH2. Patients will be instructed to exhale slowly for at least 6 s until the residual volume is reached, followed by maximal inhalation lasting at least 1.5 s. Each patient will perform at least three MIP trials, with 2-min rest intervals between attempts. The highest value will be recorded as the MIP.

**Fig. 2 Fig2:**
[figure not shown]
High-intensity interval inspiratory muscle training. **A** POWERbreathe KH2 device; **B** subjects undergoing high-intensity interval inspiratory muscle training in bed

The initial training load will be set at 50% of the MIP and will be increased by 2 cmH₂O daily. The MIP will be re-measured at the beginning of the second week, and the new training load will be determined by comparing 50% of the newly obtained MIP value with the training load achieved at the end of the first week. The starting load for the second week will be set to the higher of these two values. Each session will consist of 30 breaths divided into 5 sets of 6 breaths each, with 2-min rest intervals between sets. The participants will follow a pattern of rapid inhalation and slow exhalation. Sessions will last approximately 20 min and will be conducted once daily, 5 days per week, over a 2-week period.

Training will be paused if signs of respiratory insufficiency or hemodynamic instability are observed, defined as any of the following: respiratory rate ≥ 35 breaths/min (or > 50% above baseline), SpO₂ ≤ 90%, systolic blood pressure ≥ 180 mmHg or ≤ 80 mmHg, heart rate ≥ 140 bpm or > 20% above baseline, paradoxical breathing, agitation, depression, hemoptysis, arrhythmias, or diaphoresis [36]. If any of these criteria are met, the training intensity in the next session will not increase and will remain at the previously tolerated level.

#### Control group

The control group will follow the same evaluation protocol and follow the same training program but without any applied resistance.

### Criteria for discontinuing or modifying allocated interventions {11b}

During each training session, therapists will closely monitor vital signs and subjective symptoms. The discontinuation criteria are outlined in item 11a. Any adverse events will be documented in the daily training log. If a participant meets two or more discontinuation criteria on three consecutive training days, they will be withdrawn from the study.

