#### Primary outcome

The primary outcome of this study is the change in the MIP % predicted from baseline to the post-intervention timepoint (Week 2). MIP is a widely recognized and reliable indicator for assessing diaphragmatic function [37, 38]. Raw MIP scores were standardized according to the method of Evans and Whitelaw (males = 120 **−** (0.41** × **age); females = 108 **−** (0.61** × **age)) [39]. To account for established variations in MIP attributable to age and gender, the results are expressed as a percentage of predicted values.

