### Plans to promote participant retention and complete follow-up {18b}

During the first session, the participants will be clearly informed about the importance of attending all the scheduled sessions through the end of the study. Only those who are able to fully comply with the protocol will be enrolled. The importance of adherence will be emphasized throughout the intervention period. Participants who discontinue the study will be recorded as dropouts.

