## Statistical methods

### Statistical methods for primary and secondary outcomes {20a}

Statistical analyses will be conducted in accordance with the CONSORT guidelines to ensure methodological transparency and rigor [45]. The primary analytical approach will follow the intention-to-treat (ITT) principle, including all randomized participants irrespective of adherence to the intervention. In cases where the percentage of missing data exceeds 20%, multiple imputation will be applied using predictive mean matching for continuous variables. Sensitivity analyses will also be conducted, comparing ITT and per-protocol (PP) populations. The PP population will consist of participants who complete at least 80% of the scheduled training sessions, enabling evaluation of result robustness.

The data will be analyzed with SPSS version 26.0. The normality of continuous variables will be assessed using the Shapiro–Wilk test and visual inspection of histograms. Between-group differences in the MIP will be analyzed with independent samples *t* tests (for normally distributed data) or Mann–Whitney *U* tests (for nonnormally distributed data). The secondary outcomes will be analyzed as follows: continuous variables will be compared between groups with t tests or Mann–Whitney *U* tests on the basis of distributional assumptions. Ordinal outcomes will be evaluated with Wilcoxon rank-sum tests. Binary outcomes will be analyzed with chi-square tests or Fisher’s exact tests for small sample sizes. Adverse events will be summarized descriptively by frequency and severity.

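### Withdrawing training-intolerant participants from the study, and not only from training, probably loses their Week 2 outcome and undermines the intention-to-treat analysis

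*Protocol article*

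**What the plan says.** Item 11b (criteria for discontinuing or modifying allocated interventions) sets the rule: "If a participant meets two or more discontinuation criteria on three consecutive training days, they will be withdrawn from the study". For the criteria it points back: "The discontinuation criteria are outlined in item 11a". In item 11a, under the HI-IMT group, the same signs serve a narrower purpose: "Training will be paused if signs of respiratory insufficiency or hemodynamic instability are observed, defined as any of the following". Item 11a adds that after such a pause the load is held, not raised, at the next session.

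The arms differ in what they breathe against. For HI-IMT: "The initial training load will be set at 50% of the MIP and will be increased by 2 cmH₂O daily". Controls "follow the same training program but without any applied resistance".

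Item 18b gives the status after leaving: "Participants who discontinue the study will be recorded as dropouts". The primary outcome (item 12) is the change in MIP% predicted from baseline to Week 2.

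Item 20a describes the primary analysis as intention-to-treat, "including all randomized participants irrespective of adherence to the intervention". It calls for multiple imputation only when more than 20% of data are missing. Item 20c also calls for multiple imputation, with no threshold. The one named sensitivity analysis compares the ITT and per-protocol populations.

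**The concern.** Stopping an intervention and leaving a trial are different events. An ITT analysis needs the outcome of people who stop the intervention, because failing to tolerate it is one of the results of being assigned to it. Item 11b sits under a heading about interventions but ends participation in the study, and no section shown says that these people are still assessed at Week 2.

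The trigger is strain during training, and only one arm trains against resistance. If withdrawals fall mainly in the HI-IMT arm, and if those who cannot tolerate loading would have gained less than those who can, the comparison drifts toward the effect among people who tolerate loading. PIF, cough strength, anxiety and quality of life would be affected in the same way. An analysis plan cannot restore a measurement that was never taken.

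**Working it through.** **1. The sections side by side.** Item 11b: repeated intolerance leads to withdrawal from the study. Item 18b: leaving the study means being recorded as a dropout. Item 20a: everyone randomized is analysed, whatever their adherence. The first two remove people whom the third promises to include. The loss of the Week 2 value follows from reading 11b and 18b together; it is not stated word for word.

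**2. The plan's own figure.** Inputs from item 14: difference 8, SD 9, two-sided alpha 0.05, power 0.90, attrition 20%. With d = 8/9, the two-sample t-test needs 27.6, so 28 per group (power 0.904). Then 28/(1 − 0.20) = 35 per group. Both stated figures reproduce. The attrition allowance protects power only; it does nothing about bias from selective loss. With all 35 per group assessed, power would be 0.956.

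**3. Does the imputation rule of item 20a act?** 20% of 70 is 14, so more than 14 participants must be missing. Seven withdrawals in one arm are 7/70 = 10% overall. Even counted within the arm, 7/35 = 20% does not exceed 20%. With no other missing data, item 20a would impute nothing.

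**4. Size of the overstatement.** Assumptions: a share w of the HI-IMT arm is withdrawn, no controls are, the withdrawn would have gained only what controls gain, the retained show the planned 8 points, and nothing is imputed. Then the all-randomized difference is 8 × (1 − w), and the overstatement is 1/(1 − w) − 1.

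| Withdrawn from HI-IMT | All-randomized difference | Overstatement |
|---|---|---|
| 1 of 35 | 7.8 | 3% |
| 2 of 35 | 7.5 | 6% |
| 10% | 7.2 | 11% |
| 20% (7 of 35) | 6.4 | 25% |

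The documents give no withdrawal rate, so every row is an assumption.

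**5. Effect on the test.** Let g be the gap in mean change between retained and withdrawn HI-IMT participants. The bias is w × g. Take a true all-randomized difference of zero, SD 9 among those observed, no imputation and no control withdrawals. The standard error is 9 × √(1/n₁ + 1/35), where n₁ is the number retained, and the rejection rate comes from the noncentral t distribution.

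| Withdrawn | g = 4 | g = 8 | g = 16 |
|---|---|---|---|
| 4 of 35 | bias 0.46, rejects 5.5% | 0.91, 6.9% | 1.83, 12.8% |
| 7 of 35 | bias 0.80, rejects 6.4% | 1.60, 10.6% | 3.20, 28.2% |

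The nominal rate is 5%. The values of g are also assumptions.

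**The case against.** Several points on the other side are sound.

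- **Week 2 data.** No section says outright that withdrawn participants go unassessed. The article is condensed, and the flow chart and schedule table are not shown. This stands as a limit on certainty; the wording of 11b and 18b still points one way.
- **Imputation.** A reader might infer that the rule defeats the ITT analysis. It does not: item 20c would keep withdrawn participants in the analysis set. But standard multiple imputation assumes data missing at random, which is doubtful when intolerance of the load causes the loss, and item 20a would often not impute at all.
- **Frequency.** A reader might infer that the rule is easily met, because a rise in heart rate from 70 to 85 and in respiratory rate from 16 to 25 passes two relative thresholds (1.2 × 70 = 84; 1.5 × 16 = 24). That describes one moment. The rule needs at least two criteria, three training days running, and item 11a holds the load after any pause. Numbers may be small.
- **Who is lost.** A reader might infer that the weakest responders are removed. The criteria record tolerance during a session, not gain in MIP, and some, such as agitation or arrhythmia, could occur in controls. Predominance in the loaded arm is plausible but not shown.
- **Safety.** The events that trigger withdrawal are recorded in the daily training log. Only later events are uncertain.
- **Feasibility.** Measuring MIP takes at least three maximal efforts. Some withdrawn participants may not be able to do this, so some data may stay missing.

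**Conclusion.** The point holds as a conflict between items 11b and 18b on one side and item 20a on the other, made worse by the differing imputation rules in 20a and 20c. Followed as written, the rule probably creates missing primary data that may depend on arm and on outcome. It undermines the ITT analysis and does not nullify it.

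The size cannot be known from the documents. One or two withdrawals in the HI-IMT arm would be a minor distortion (about 3% or 6%). At 10% or 20% of the arm it would matter (11% or 25%), and with 7 of 35 withdrawn and an 8-point gap the false-positive rate would be about 10.6%. These figures rest on one-sided withdrawal, no imputation, and the stated assumption about what withdrawn participants would have gained. The per-protocol comparison would not reveal the problem, because both populations would lack the same outcomes.

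**What to change.** Reconcile items 11b, 18b, 20a and 20c:

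- In 11b, let the rule end training, not study participation. State that these participants stay in follow-up, have the planned blinded Week 2 assessment where consent continues and the clinician judges it feasible, and have adverse events followed to the end of the study period.
- In 18b, keep the term dropout for those who withdraw consent or cannot be assessed. Record the reason, and record separately when training stopped.
- In 20a and 20c, state that participants who stop training are analysed in their randomized arm, and give one rule for imputation.

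The thresholds for pausing or stopping training stay as they are; no view is taken on them.

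The cost is a short amendment and a few assessments that are already scheduled, some of which may prove infeasible. Recruitment began in August 2025, so a Week 2 value missed before the amendment cannot be recovered.

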### Adverse event reporting and harms {22}

Although this study is associated with minimal known risks, participants are instructed to immediately notify the responsible physiotherapist of any adverse or serious events. The possible side effects may include fatigue, dizziness, or transient decreases in blood oxygen saturation. Any adverse events will be promptly reported to the Institutional Research Ethics Committee by the designated principal investigator.

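### The only stated mandatory withdrawal rule counts signs without grading them, so one serious sign recurring at all 10 sessions never meets it, and it removes participants from the study rather than from training

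*Protocol article*

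**What the plan says.** Item 11a (Intervention description, HI-IMT group) sets the signs that pause a session. They are limits on respiratory rate, SpO₂ (90% or less), systolic pressure and heart rate, the last being 140 beats/min or a relative rise, with the list ending "20% above baseline, paradoxical breathing, agitation, depression, hemoptysis, arrhythmias, or diaphoresis". Any one sign is enough to pause, and no sign ranks above another. The stated consequence is that "the training intensity in the next session will not increase and will remain at the previously tolerated level".

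Item 11b calls the same list the discontinuation criteria and adds: "If a participant meets two or more discontinuation criteria on three consecutive training days, they will be withdrawn from the study". It also says that "Any adverse events will be documented in the daily training log".

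The HI-IMT sessions take place "under the guidance of a trained physiotherapist". Under item 22, "participants are instructed to immediately notify the responsible physiotherapist of any adverse or serious events", and "Any adverse events will be promptly reported to the Institutional Research Ethics Committee by the designated principal investigator". Item 21a gives safety monitoring to the coordinating center, without an independent monitoring committee. Item 23 has the steering committee audit biweekly, including recorded adverse events.

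Item 20a bases the primary analysis on all randomized participants, whatever their adherence. Item 18b records those who discontinue as dropouts.

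**The concern.** A stopping rule should respond at least as strongly to a graver event as to a milder one. This rule responds to the number of signs. Two signs that effort alone can produce, a raised heart rate and sweating, compel withdrawal if they persist for three training days. One sign that most clinicians would regard as serious, such as hemoptysis, never does. Because the text fixes the load for the following session, it also presumes that there will be one, and no stated step decides whether there should be.

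What is at stake is patient safety in weak patients (entry requires MIP of at most 30% predicted) whose load is planned to rise by 2 cmH₂O a day.

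A second issue sits in the same sentence. Ending training and leaving the study are treated as one event. Read literally, a participant who cannot tolerate training also loses the Week 2 assessment that the intention-to-treat analysis needs.

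**Working it through.** The plan gives no figure of its own on this point, so the check applies the stated rule to possible courses of events.

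**Inputs**
- Sessions: once daily, 5 days a week for 2 weeks (item 11a), so 5 × 2 = 10.
- Signs: ten, counting each vital-sign item once with all its limits (respiratory rate, SpO₂, systolic pressure, heart rate, paradoxical breathing, agitation, depression, hemoptysis, arrhythmias, diaphoresis).
- Rule: at least two signs on each of three training days in a row (item 11b).
- Entry condition: "heart rate between 60 and 120 beats/min" (item 10). Baseline heart rate is assumed to lie in this range.

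**Applying the rule**

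| Course of events | Rule met? |
|---|---|
| One sign at all 10 sessions | No: the daily count is 1 |
| Any of the 2^10 = 1,024 on/off patterns of a single sign | No, in none |
| Hemoptysis plus SpO₂ ≤ 90% at sessions 1 and 2 only | No: the run is 2 days |
| Two signs on two days, one on the next, repeated (two signs on 7 of 10 days) | No: the run never reaches 3 |
| Raised heart rate plus diaphoresis at sessions 1 to 3 | Yes, at session 3 |

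Session 3 is the earliest point at which the rule can apply, whatever the signs.

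**Heart-rate item.** The relative limit is 1.2 × baseline:
- baseline 60: 1.2 × 60 = 72, so 73 beats/min meets it;
- baseline 80: 1.2 × 80 = 96;
- baseline 117: 1.2 × 117 = 140.4, so the fixed limit of 140 is reached first.

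For a participant with a low baseline, a modest rise during effort therefore counts the same as hemoptysis.

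**Do the other safeguards decide on the next session?**
- Pause and held load (11a): they act on the current session and cap the next load, but do not decide whether it takes place.
- Training log (11b) and ethics committee report (22): these record and notify.
- Coordinating center (21a): no trigger or timing is stated.
- Steering committee audits (23): if biweekly means every two weeks, the interval equals the whole course.
- Unblinding after a serious adverse event (17b): governs disclosure of allocation.
- Voluntary withdrawal (26a): the participant's choice.

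**Withdrawal against the analysis set.** Item 11b removes the participant from the study and item 18b counts discontinuers as dropouts, while item 20a promises an analysis of everyone randomized. An outcome that could have been measured at Week 2 would become a missing value.

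**The case against.** The strongest reply is that the count rule is only a back-stop. The working safeguard is in item 11a, where any one sign pauses the session and stops the load from rising, so a participant with hemoptysis at every session would be paused every time. Training takes place in a hospital, in a treatment room or at the bedside, alongside conventional medical care. Item 17b envisages serious adverse events that need immediate intervention, and item 5d charges the steering committee with ongoing oversight of safety. The article is also a condensed account, and a physician's review of adverse events may well be set out in the full protocol.

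Much of this stands, and it rules out several stronger readings:
- A reader might infer that one serious sign has no consequence, or that clinicians may not stop training earlier. Neither is so: the pause and the load cap apply, and item 11b does not forbid earlier stopping.
- A reader might infer that no physician is ever involved. The article's silence does not show that.
- A reader might infer that a sign at session 1 leaves the load for session 2 undefined. The bar on an increase makes the session 1 load the ceiling; only a reduction below it is left unstated.
- A reader might want every SpO₂ reading of 90% or less treated as serious. Item 22 expects short-lived desaturation, and entry allows an SpO₂ of 93%, so a brief fall of 3 points would qualify.

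The documents do not rank the signs, so calling hemoptysis and new arrhythmia serious is a clinical judgment that the sponsor's clinicians should confirm.

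What the reply does not answer is the rule that the article does state. Its threshold is a bare count, and the instruction after a sign assumes that training goes on.

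**Conclusion.** The point holds as a badly set rule, not as a missing one. A single serious sign can recur at 10 of 10 sessions without meeting the only stated mandatory withdrawal criterion, while two signs that effort can produce meet it at session 3. The wording also takes participants out of the study, against the intention-to-treat analysis in item 20a.

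This assumes that the rule means at least two different signs on each of three successive training days, which is its natural sense, and that baseline heart rate lies in the entry range. In practice serious signs may occur together, and clinicians may act sooner. That affects how often the gap would matter, which cannot be estimated because no event rate is given. No effect on the primary estimate is claimed. The change is worth making for safety and for clarity of follow-up.

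**What to change.** Amend items 11a and 11b as follows:

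1. Keep the present list as criteria for pausing a session, and set separate criteria for ending training.
2. Require review by an existing study or treating physician before the next session, with authority to end training, after hemoptysis, a new arrhythmia, or SpO₂ of 90% or less that is sustained or recurs. A brief transient fall should not trigger review.
3. Keep the two-sign, three-day rule as an additional trigger.
4. Replace withdrawal from the study with discontinuation of training, and state that Week 2 outcomes are still collected and analyzed in the randomized group.

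The cost is a short amendment, with the ethics approval and registry update that item 25 requires, and brief retraining of therapists. The number of physician reviews is unknown, since the documents give no event rate. Some participants may stop training earlier than under the present text, but their outcomes would be kept.
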